### Clinical outcomes

#### Primary outcome

Cardiorenal anemia syndrome (CRAS) is the primary outcome of this study and will be defined as a triad comprising heart failure regardless of ejection fraction, chronic kidney disease with estimated glomerular filtration rate <60mil/min/1.73m^2^ and anemia of <12 g/dl for women or <13 g/dl for men [1, 2].

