#### Secondary outcomes

Secondary outcomes will include:

**All-cause mortality** is any death that will occur within follow-up irrespective of cause [2, 11, 17–19].**Heart failure hospitalization** is defined as any admission of which the cause-specific is heart failure [2, 3, 5, 6].**Worsening renal function**: is defined when there is a change in chronic kidney disease stage to lower stage than baseline or a need of a dialysis or both [20, 21].**Worsening anemia**: is defined when there is a change of hemoglobin level to lower level from baseline which will then need either blood transfusion or erythropoietin use or both [3, 5, 22, 23].

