**Chronic kidney disease (CKD)**	Medical records/patient report	Known patient with CKD from medical records within 6 months retrospectively prior enrollment or when estimated GFR is <60mil/min/1.73m2 by CKD-EPI formula using serum creatinine level	Dichotomous, continous
**Dyslipidemia**	Medical records/patient report/blood sample	Evidence of dyslipidemia on medications from records or for unknown lipid status, when the total cholesterol ≥200 mg/dl, low-density lipoprotein cholesterol ≥130 mg/ dl, and high-density lipoprotein cholesterol < 40 mg/ dl for men or < 50 mg/ dl for women, and/or serum triglyceride level ≥150 mg/ dl	Dichotomous, categorical
**Diabetes**	Medical record/patient report/blood sample	Known patient with diabetes mellitus on medications from records or for unknown status, is when the random blood glucose is ≥11.1 mmol/L and glycosylated haemoglobin of ≥6.5%	Dichotomous, categorical
**Electrolyte imbalance**	Medical report/blood sample	Serum Na+ of <135mmol/L or >145mmol/L and/or serum K+ of < 3.5mmol/L or >5.5mmol/L	Continous
**Obesity**	Medical record/patient assessment	When the waist circumference of >94 cm for males or >88 cm for females; or calculated waist-hip ratio (WHR) of >0.9 for men or of >0.8 for women	Dichotomous, categorical

#### Objective 3

Aims to determine the outcomes of the cardiorenal anemia syndrome among the patients with heart failure within six months follow up period [2, 5, 7, 11, 25] Table 3.

**Table 3 pone.0292764.t003:** Summary and description of variables for the objective number 3.

Variable	Method of measurement	Operational definition	Level of measurement
**All-cause mortality**	Medical records or close relative through phone contact	Any death occurs within six month follow up irrespective of the cause of death	Dichotomous
**Heart failure hospitalization**	Medical record/patient report/assessment	admission of which cause-specific is heart failure	Continuous
**Worsening renal function**	Medical record/patient report/blood sample	When there is a change in Chronic kidney disease stage or a need of dialysis or both	Continuous
**Worsening anemia**	Medical record/patient assessment/blood sample	Change of hemoglobin level to lower level from baseline or a need of blood transfusion or erythropoietin use or both	Continuous

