### Data collection process

#### Evaluation of the participants

A minimum of 300 patients who meet the inclusion criteria will be enrolled in this study from 18^th^ August, 2023 to 18^th^ April, 2024 including 3-months of enrollment and a 6-month of follow up. Follow-up period will be done on monthly basis via phone calls or through routine clinic visits to assess for the secondary outcomes. Data will be collected using a well-structured questionnaire, which will include socio-demographic information, physical examination and anthropometry, assessment of underlying comorbid conditions, laboratory investigations, and non-invasive cardiac imaging. Socio-demographic data will include age, gender, smoking history, history of alcoholic use either current or previous case, and anthropometric measurements including waist circumference, hip circumference and then, waist-hip ratio will be calculated [28]. Focused clinical history will be exhausted to assess the symptoms related to heart failure using modified Framingham criteria. Two major criteria or one major and two minor criteria will be sufficient to make a diagnosis of heart failure [29]. Subjective Functional status by using New York Heart Association functional criteria will be recorded, which comprises four classes as follows [2, 12, 30]: class 1 means no limitation to physical activities, class 2 means slight limitation to strenuous activities, class 3 means marked limitation to simple and slightly activities and class 4 means symptoms at rest.

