#### Follow-up procedure

Every patient will be followed up on monthly basis within 6-months via phone calls or during regular clinic visit. In case a participant is not reachable following 3 phone calls on 3 alternative days on every fourth week of follow-up month or during clinic visit. Failure to be reachable will indicate lost to follow-up.

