### Data analysis

All completed questionnaires will be coded before entered into dataset on Microsoft excel. SPSS windows version 25 program (IBM SPSS, Chicago IL) will be used for data management and analysis [16]. Data will be classified as CRAS or non-CRAS groups. Data will be presented as means **±** standard deviations for continuous variables with normal distribution, or median and interquartile range for no-parametric (skewed) variables [1, 2, 13]. Categorical variables will be presented as frequencies and percentages. Socio-demographic variables and clinical correlates of cardiorenal anemia syndrome at baseline will be analyzed and compared using Pearson chi-squared test for the categorical variables, and independent student’s t-test for the continuous variables [1, 2, 9]. The clinical correlates including age, gender, alcohol use, smoking history, hypertension, obesity, diabetes, and dyslipidemia and iron deficiency will be analysed and compared by using univariate and multivariate logistic regression. Cox proportional hazards model will be used to analyze and compare the outcomes of CRAS. A two-tailed p—value of less than 0.05 will indicate statistical significance [2, 7, 13].

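### Heart failure hospitalization depends on the cause of admission, but Table 3 accepts patient report as a source, so admissions for other causes can be miscounted and bias the Cox hazard ratio in either direction

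*Protocol article*

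**What the plan says.** Under Secondary outcomes, the protocol article defines heart failure hospitalization as "any admission of which the cause-specific is heart failure". Table 3 (Study variables, Objective 3) repeats the definition as "admission of which cause-specific is heart failure". The method-of-measurement cell for this outcome reads "Medical record/patient report/assessment".

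Evaluation of the participants describes how the outcome is collected: "Follow-up period will be done on monthly basis via phone calls or through routine clinic visits to assess for the secondary outcomes". Follow-up procedure repeats the monthly schedule and again allows either mode of contact.

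The exposure is defined under Primary outcome as heart failure with "chronic kidney disease with estimated glomerular filtration rate <60mil/min/1.73m^2^ and anemia of <12 g/dl for women or <13 g/dl for men". Under Data analysis, "Cox proportional hazards model will be used to analyze and compare the outcomes of CRAS".

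**The concern.** Whether an admission happened is something a patient can usually report. Whether it was caused by heart failure, by renal failure with fluid overload, or by anaemia needing transfusion is much harder for the patient to say. A person who knows they have heart failure may describe any of these as a heart failure admission. As the table stands, nothing prevents that description, given by phone, from becoming the recorded event.

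The error need not be equal in the two groups. CRAS patients have anaemia and reduced eGFR by definition, and the Introduction lists worsening anemia and worsening renal function among the common outcomes of CRAS. The worsening outcomes are themselves defined partly through dialysis and transfusion, either of which can bring a patient into hospital. If other-cause admissions are more frequent in CRAS, false events fall unequally across the comparison, and the hazard ratio for this Objective 3 outcome is distorted by an amount and in a direction that the data cannot reveal afterwards.

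**Working it through.** The article states no admission rate, hazard ratio or event count for this outcome, so there is no plan figure to reproduce. The check asks when misreporting moves the hazard ratio, and by how much.

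**Inputs.** From the article: the cause-specific definition, the accepted sources, the phone or clinic contact, the six-month follow-up and the Cox comparison. Assumed, because the article does not give them:
- h, the true six-month risk of heart failure admission: 20-30% in non-CRAS
- o, the six-month risk of an admission for another cause: 10-25% in CRAS, 5-10% in non-CRAS
- m, the share of other-cause admissions reported as heart failure: 20-60%, equal in both groups

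**Formula.** Observed risk = h + (1 - h) × o × m. Apparent hazard ratio = ln(1 - observed risk in CRAS) / ln(1 - observed risk in non-CRAS).

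**No true difference (h equal in both groups).**
- h = 0.20, o = 0.15 v 0.05, m = 0.40. CRAS: 0.20 + 0.80 × 0.15 × 0.40 = 0.248. Non-CRAS: 0.20 + 0.80 × 0.05 × 0.40 = 0.216. Ratio: ln(0.752)/ln(0.784) = 1.17.
- Largest in the assumed ranges: h = 0.20, o = 0.25 v 0.05, m = 0.60. Risks 0.320 v 0.224; ratio ln(0.680)/ln(0.776) = 1.52.
- Smallest: o = 0.10 in both groups. Risks are equal and the ratio is 1.00.

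**True hazard ratio 2.** With h = 0.20 in non-CRAS, the true risk in CRAS is 1 - 0.80² = 0.36. Take m = 0.40.
- o = 0.10 v 0.05: risks 0.3856 v 0.2160; ratio ln(0.6144)/ln(0.7840) = 2.00, no bias.
- o = 0.15 v 0.10: risks 0.3984 v 0.2320; ratio ln(0.6016)/ln(0.7680) = 1.93, biased downward although other-cause admissions are commoner in CRAS.
- Over the full assumed ranges, the lowest value is at o = 0.10 v 0.10, m = 0.60: ln(0.6016)/ln(0.7520) = 1.78. The highest is at o = 0.25 v 0.05, m = 0.60: ln(0.5440)/ln(0.7760) = 2.40.

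**Condition for the direction.** On the rate scale, the apparent hazard ratio is (h1 + m × g1)/(h0 + m × g0), where h is now the heart failure admission rate, g the rate of other-cause admissions, 1 is CRAS and 0 is non-CRAS. This is a weighted average of the true hazard ratio h1/h0 and the ratio g1/g0. It exceeds the true value only when g1/g0 does. With h0 = 0.20, g0 = 0.05-0.10 and m = 0.10-0.50:
- true hazard ratio 1.0, g1/g0 from 1 to 3: 1.00 to 1.40
- true hazard ratio 1.5, g1/g0 from 1 to 3: 1.40 to 1.80
- true hazard ratio 2.0, g1/g0 = 1.5: 1.90 to 1.99

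**Missed events.** Patient report can also fail to identify a true heart failure admission. With a true hazard ratio of 1.5, capturing 80% of true events in CRAS and 90% in non-CRAS gives 1.5 × 0.8/0.9 = 1.33. The reverse gives 1.5 × 0.9/0.8 = 1.69.

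**The case against.** **The table may only list sources.** The column is a template of data sources. The medical record stands first, assessment is also listed, and the cell does not say that patient report alone decides the cause. Table 3 names phone contact only for mortality, so classification by phone is put together from two sections. This is fair as a reading of intent. As written, however, the sources are alternatives with no ranking. The same table omits patient report for worsening anemia, so the sources do vary by outcome.

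**Detail may sit elsewhere.** Adjudication rules and blinding of assessors may be in a fuller protocol or analysis plan, and their absence from an article is no finding. That stands. The point rests on what the article does state: patient report is an accepted source for an outcome defined by cause.

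**A reader might infer that the hazard ratio is inflated.** The documents do not support that. More renal or anaemia admissions in CRAS are not enough; their ratio must exceed the true heart failure hazard ratio. The Introduction lists heart failure hospitalization among the common outcomes of CRAS, so the authors do not expect equal hazards. The inclusion criteria also list chronic kidney disease. If the criteria apply jointly, non-CRAS patients have it too, the renal part of the argument weakens, and anaemia is the main difference left.

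**The record is not perfect either.** Fluid overload in a patient with both heart and kidney disease can be ambiguous in a discharge summary. That also stands: record confirmation reduces the error but does not abolish it.

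**Conclusion.** The point holds as a risk of misclassification that can differ between the groups and whose direction is uncertain. The bias is upward if misreported admissions are more concentrated in CRAS than true heart failure admissions, and nil or downward otherwise. Under the assumed ranges the apparent hazard ratio is 1.00 to 1.52 when there is no true difference, and 1.78 to 2.40 when the true value is 2. Every rate behind these figures is an assumption, as are an equal misreporting share in both groups and other-cause admissions arising independently of heart failure admissions. The figures show possible size and are not estimates for this study. It concerns one secondary outcome, and the remedy is a cheap improvement.

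**What to change.** In Table 3, let patient or relative report serve only to detect that an admission took place. Count it as heart failure hospitalization when the hospital record or discharge summary gives heart failure as the cause, read by the existing team without reference to CRAS group. Keep admissions whose record cannot be obtained as 'cause unverified', and show the Cox result with them excluded and with them included.

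The medical record is already a listed source, so no new data source is needed. The cost is one record look-up per reported admission and one further analysis. Some admissions to other hospitals will stay unverified, so the confirmed count will be slightly smaller.

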### Participants’ characteristics

Participants are adults of 18 years or older attending internal medicine, cardiology and nephrology departments of the Benjamin Mkapa hospital in Dodoma who met the study criteria [4, 26, 27].

### Data collection process

#### Evaluation of the participants

A minimum of 300 patients who meet the inclusion criteria will be enrolled in this study from 18^th^ August, 2023 to 18^th^ April, 2024 including 3-months of enrollment and a 6-month of follow up. Follow-up period will be done on monthly basis via phone calls or through routine clinic visits to assess for the secondary outcomes. Data will be collected using a well-structured questionnaire, which will include socio-demographic information, physical examination and anthropometry, assessment of underlying comorbid conditions, laboratory investigations, and non-invasive cardiac imaging. Socio-demographic data will include age, gender, smoking history, history of alcoholic use either current or previous case, and anthropometric measurements including waist circumference, hip circumference and then, waist-hip ratio will be calculated [28]. Focused clinical history will be exhausted to assess the symptoms related to heart failure using modified Framingham criteria. Two major criteria or one major and two minor criteria will be sufficient to make a diagnosis of heart failure [29]. Subjective Functional status by using New York Heart Association functional criteria will be recorded, which comprises four classes as follows [2, 12, 30]: class 1 means no limitation to physical activities, class 2 means slight limitation to strenuous activities, class 3 means marked limitation to simple and slightly activities and class 4 means symptoms at rest.

#### Measurements of clinical variables

*Waist circumference*. Is the measurement of the abdominal girth in centimeters and will be measured in erect position with abdomen relaxed and arms aside and will be recorded over the unclothed relaxed abdomen at the smallest diameter between the coastal margin and the iliac crest of which >94 cm for men and >88 cm for women will be defined as central obesity. In addition, hip circumference in centimeter will be recorded over minimal clothing at the level of the greater trochanter (usually the widest diameter around the buttocks). Waist-hip ratio (WHR) is dimensionless measurement and will be calculated from waist circumference and hip circumference. A WHR ≥0.9 or ≥0.8 will indicate obesity. The sensitivity and specificity of waist-hip ratio of more than 85% compared to body mass index (BMI) in predicting obesity [28, 31].

*Blood pressure measurement*. A blood pressure (BP) reading will be measured by the conventional method by using a calibrated automated BP machine keeping with the 2018 AHA/ACC hypertension guideline for standard measurement of BP. The patient should be required to empty the urinary bladder prior to measurement, not to smoke, not take alcoholics or caffeine nor strenuous exercises within 30 minutes prior to measurement. Three BP readings will be taken in relaxed position 3 to 5 minutes apart per each reading and an average of the last two BP readings will be used. Blood pressure ≥ 140/90 mmHg will be defined as hypertension [2, 16, 32].

#### Laboratory and imaging investigations

*Collection of blood sample*. The laboratory standard operating procedures accredited and supervised by the Benjamin Mkapa hospital will be warranted throughout the study. Each participant will consent for venipuncture which will inflict pain during sample collection, then laboratory technician will follow the aseptic procedures during sample collection. Before sample collection, collecting tubes (purple toped EDTA (K2/ K3) sodium fluoride plain with additive and another red toped plain tubes, with no additive) will be labeled with the patient’s particulars. The tourniquet will be applied 30 to 60 centimeters above elbow joint. The intended site of venipuncture will be cleaned with 70% methylated spirit and the area is left to dry for 15 to 20 seconds before venipuncture. Then 10 mls of venous blood will be taken using a 10-cc syringe.

The tourniquet will be released and removed, and the site of venipuncture will be compressed with a cotton swab for 1 to 5 minutes to arrest bleeding. From the samples, the following tests will be analyzed: lipid profile (high density lipoprotein-cholesterol, low density lipoprotein-cholesterol, total cholesterol and serum triglycerides), full blood picture (haemoglobin level, mean corpuscular volume, mean corpuscular hemoglobin), Iron studies (serum iron, serum ferritin, total iron binding capacity and transferrin saturation), high-sensitive C-reactive protein, and serum creatinine and serum electrolytes (serum sodium and serum potassium). The cool box will be used for transportation of samples to the BMH laboratory for processing 15 to 30 minutes after sample collection. The serum sample will be separated from whole blood by centrifugation at 300 rpm for 5 minutes, and two aliquots will be prepared. A sample is stored at 2°c—8°c if the analysis is expected after 2 hours from sample collection especially for iron studies which be analyzed after every 100 collected samples using MAGLUMI 800 CLIA. However, blood samples will be stored at room temperature if the analysis is expected to be done within 2 hours from time of sample collection. Analysis of the sample will be done using clinical chemistry automatic analyzer MAGLUMI 800 CLIA made in China, 2019 and Roche Cobas 6000 CLIA made in USA, 2018.

*Lipid profile*. Dyslipidemia is defined as total serum cholesterol ≥200 mg/dL, or LDL-cholesterol ≥130 mg/dL, or serum triglyceride ≥150 mg/dL, or HDL-cholesterol <40 mg/dL for women and <50 mg/dL for men [16, 33].

*Blood sugar measurement*. Diabetes mellitus will be defined as either known patient with type 1 or 2; and for unknown diabetic status, is when random blood glucose by using blood from finger prick is ≥11.1mmol/L and glycated hemoglobin is ≥6.5% [14, 34].

*Iron studies*. Iron deficiency will be defined as serum ferritin of <100μg/l and high sensitive C-reactive protein of ≥ 3 mg/dl [35], or serum ferritin of 100 to 300 μg/l and transferittin saturation (TSAT) ≤ 20% [7, 10–12, 36].

*Full blood picture*. Anemia will be defined when hemoglobin ≤ 12g/dl for women or ≤ 13g/dl for men. Mean Corpuscular Volume (MCV) and Mean Corpuscular Hemoglobin (MCH) will be recorded to characterize the type of anemia [2, 12, 16].

*Serum electrolytes*. Electrolyte imbalance will be considered when the serum sodium is ≤ 135 mmol/l (hyponatremia) or ≥ 145mmol/l (hypernatremia) and / or potassium level of ≤ 3.5mmol (hypokalemia) or ≥ 5.3 mmol/l (hyperkalemia) [20, 33, 37].

*Blood creatinine*. Chronic kidney disease will be defined following estimation of glomerular filtration rate. Glomerular Filtration Rate will be calculated by using CKD-EPI formula by adjustment of African-American correction factor and value of <60mil/min/1.73m2 will be considered as chronic kidney disease [34, 37, 38].

*Two-dimension transthoracic echocardiogram (2D-TTE)*. Transthoracic Echocardiography (model Vivid TM T9 manufactured by GE Healthcare, USA 2018) will be used for recommended patients who are either newly diagnosed patients or for previous known HF patients of which their echocardiogram reports are of more than 6-months prior to index contact. Transthoracic Echocardiogram will be done by experienced echocardiographer and/or confirmed by consultant cardiologists. Depending on condition of the patient so, a patient will be instructed to undress and expose the chest then, the patient will lie on the left lateral decubitus position and then, change to supine position during imaging for different echocardiogram views. The imaging will take 10 to 20 minutes.

During imaging, the confidentiality and privacy will be warranted. Findings of potential diagnostic importance will be extracted from the echocardiogram report which will include diastolic dysfunction of either grade, elevated left atrial pressure and left ventricular ejection fraction [26].

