### Study variables

#### Objective 1

Aim to determine the prevalence of cardiorenal anemia syndrome among patients with heart failure irrespective of ejection fraction at baseline Table 1.

**Table 1 pone.0292764.t001:** Summary and description of objective number 1 variables of the study.

Variable	Method of measurement	Operational definition	Level of measurement
CRAS	Patient assessment/medical or echocardiographic records/blood sample	Heart failure with ejection fraction of <50% or >50%, chronic kidney disease with estimated glomerular filtration rate <60mil/min/1.73m^2^ and anemia with hemoglobin of <13 g/dl for men or <12 g/dl for women	Dichotomous

#### Objective 2

Aims to determine the clinical correlates for the cardiorenal anemia syndrome at baseline among the patients with heart failure irrespective of ejection fraction [2, 6, 24, 25]. Information from medical records such as chronic kidney disease using serum creatinine level and echocardiographic report will be accessed from 18^th^ February, 2023 onwards. Table 2.

**Table 2 pone.0292764.t002:** Summary and description of variables for the objective number 2.

Variable	Method of measurement	Operational definition	Level of measurement
**Age**	Medical records/patient	Age in years	Continuous
**Gender**	Medical record/patient report	Male versus female	Dichotomous, categorical
**Alcoholic use**	Patient report, interview	Use of alcoholics regardless of amount/units, years or number of drinks per day	Dichotomous, categorical
**Anemia**	Blood sample	When hemoglobin level is <13 g/dl for men or <12 g/dl for women	Dichotomous, continous
**Iron deficiency**	Blood sample	Serum ferritin of <100μg/l and high sensitive C-reactive protein of ≥3 mg/dl; or serum ferritin of 100 to 300 μg/l and calculated transferittin saturation (TSAT) of < 20% will indicate iron deficiency	Dichotomous, continous
**Hypertension**	Medical records/patient report/ patient assessment	Known hypertensive patient from records; or measurement of BP readings by conventional method using digitalized calibrated Blood pressure machine adhered on standard operating procedures and when the average of last two readings taken in between 3 minutes apart is ≥ 140/90mmHg will indicate hypertension	Dichotomous, categorical

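### The laboratory section contradicts the primary outcome definition on the anaemia boundary, and Table 2 on the HDL cut-offs by sex and on how the dyslipidaemia criteria combine

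*Protocol article*

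**What the plan says.** **Anaemia.** The Primary outcome section defines the haemoglobin limb of CRAS as "anemia of <12 g/dl for women or <13 g/dl for men". Table 1 (Study variables) repeats it as "anemia with hemoglobin of <13 g/dl for men or <12 g/dl for women", and Table 2 as "When hemoglobin level is <13 g/dl for men or <12 g/dl for women". Under Laboratory and imaging investigations, the full blood picture paragraph instead reads "Anemia will be defined when hemoglobin ≤ 12g/dl for women or ≤ 13g/dl for men".

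**HDL.** Table 2 has "high-density lipoprotein cholesterol < 40 mg/ dl for men or < 50 mg/ dl for women". The lipid profile paragraph of the laboratory section has "HDL-cholesterol <40 mg/dL for women and <50 mg/dL for men".

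**Combining the lipid criteria.** Table 2 lists total cholesterol, LDL *and* HDL, then attaches triglyceride with *and/or*. The laboratory section puts *or* between all four. Table 2 also counts patients whose records show dyslipidaemia on medication; the laboratory section does not mention them.

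**Use.** The Data analysis section splits the data into CRAS and non-CRAS groups. It names dyslipidaemia and gender among the correlates for univariate and multivariate logistic regression.

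**The concern.** A woman with haemoglobin of exactly 12.0 g/dl, or a man with exactly 13.0 g/dl, is anaemic under one section and not under the others. If eGFR is also below 60, that decides whether the patient counts as CRAS.

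A patient with HDL between 40 and 50 mg/dl meets the HDL criterion under one section and not under the other, and which section counts the patient depends on sex. The connector decides whether one abnormal lipid fraction is enough or several are needed.

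Data management and Data analysis both say that questionnaires are coded before data entry, so the section a coder follows could fix the recorded value. At stake are the prevalence estimate, by a small amount, and the dyslipidaemia covariate, possibly by a good deal more. An unresolved conflict also leaves room to choose a definition after results are seen.

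**Working it through.** The plan gives no figure to reproduce here. The contradictions are established by setting the sections side by side; the arithmetic only sizes them. The documents report no haemoglobin or lipid distribution, so every distribution below is an assumption shown over a range.

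| Item | Primary outcome, Tables 1–2 | Laboratory section |
|---|---|---|
| Anaemia, women / men (g/dl) | <12 / <13 (primary outcome and both tables) | ≤12 / ≤13 |
| Low HDL, men / women (mg/dl) | <40 / <50 (Table 2) | <50 / <40 |
| Lipid criteria | TC, LDL *and* HDL, *and/or* TG (Table 2) | TC *or* LDL *or* TG *or* HDL |
| On lipid medication | counted (Table 2) | not mentioned |

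**1. Anaemia boundary.** Assume haemoglobin is recorded to 0.1 g/dl and is normal with mean m = 11 to 13 and SD s = 1.5 to 2.5. The share exactly on cut-off c (12 or 13) is Φ((c + 0.05 − m)/s) − Φ((c − 0.05 − m)/s).
- Smallest (c = 13, m = 11, s = 1.5): 0.0109.
- Largest (m = c, s = 1.5): 0.0266.
- Of 300 patients: 300 × 0.0109 ≈ 3 to 300 × 0.0266 ≈ 8.

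This is the change in anaemia status. It is an upper bound for CRAS, which also requires eGFR below 60. For scale, the 95% half-width at the plan's expected prevalence of 40% with 300 patients is 1.96 × √(0.40 × 0.60 / 300) = 0.055, or 5.5 points.

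**2. HDL criterion.** Assume HDL is normal with mean m = 40 to 50 and SD s = 10 to 15 mg/dl. The share between the two cut-offs is Φ((50 − m)/s) − Φ((40 − m)/s).
- Smallest (m = 40 or 50, s = 15): 0.248.
- Largest (m = 45, s = 10): 0.383.

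Going from Table 2 to the laboratory section, men in this band become low-HDL and women in it stop being low-HDL.

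**3. From HDL to dyslipidaemia.** Under the all-*or* rule, a patient in the band changes dyslipidaemia status only if none of the other three criteria is met. If each is met with probability p, independently, that is (1 − p)³:
- p = 0.2: 0.8³ = 0.51
- p = 0.3: 0.7³ = 0.34
- p = 0.4: 0.6³ = 0.22

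As a share of all patients this runs from 0.248 × 0.22 ≈ 0.05 to 0.383 × 0.51 ≈ 0.20. If Table 2 is read as (TC and LDL and HDL) or TG, the patient must meet TC and LDL and not TG, with probability p²(1 − p) = 0.03, 0.06 or 0.10. The effect is then much smaller.

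**4. Connector.** Let each of the four criteria be met with probability p, independently.

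| p | all *or*: 1 − (1 − p)⁴ | (TC and LDL and HDL) or TG: 1 − (1 − p³)(1 − p) | all four: p⁴ |
|---|---|---|---|
| 0.2 | 59% | 21% | 0.2% |
| 0.3 | 76% | 32% | 0.8% |
| 0.4 | 87% | 44% | 2.6% |

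Real lipid criteria are correlated. Positive correlation would narrow these gaps and would raise the step 3 figures for the *or* rule somewhat.

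**The case against.** The strongest reply is that little of this reaches the primary outcome. The section headed as the primary outcome and both tables agree on the strict inequality, so the laboratory section is the outlier and a careful analyst would follow the other three. The shift is at most about 1–3 points against a half-width of 5.5. That stands as to size. It does not remove the contradiction, and a boundary rule shifts the estimate in one direction, which a larger sample would not average out.

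A reader might take the share with low HDL as the share with dyslipidaemia and conclude that a quarter or more of patients are misclassified on the covariate. The documents do not support that. Dyslipidaemia is a composite, and under the *or* rule only patients with no other abnormal fraction change status; under Table 2, patients on lipid medication count whatever their HDL.

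A reader might also infer that the gender odds ratio is necessarily distorted. That depends on how dyslipidaemia relates to CRAS, which the documents do not give, so only a possible bias can be claimed.

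Table 2's *and* followed by *and/or* can be read as a loose list rather than a strict conjunction. That is fair: the wording is ambiguous rather than a clear *and* rule. An ambiguous rule beside an explicit *or* rule still needs resolving.

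Two further discrepancies are minor. The sodium and potassium limits differ (for example, hyperkalaemia above 5.5 in Table 2, but from 5.3 upward in the laboratory section), yet electrolyte imbalance is not among the correlates named for the regression. Table 1's ejection fraction wording omits exactly 50%, but the inclusion criteria and the primary outcome admit any ejection fraction, so no patient is lost.

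**Conclusion.** The point holds. Anaemia, HDL and the dyslipidaemia rule are each stated in two incompatible ways in the current text. The anaemia conflict touches the primary outcome but moves few patients: about 1–3% for anaemia and no more than that for CRAS, given haemoglobin SD 1.5–2.5 g/dl recorded to 0.1. The HDL and connector conflicts affect a covariate only, but could reclassify more patients. The HDL criterion flips for about 25–38% (mean 40–50, SD 10–15 mg/dl). Dyslipidaemia status changes for about 22–51% of those under the *or* rule, if each other criterion is met by 20–40% independently. Because the flip runs in opposite directions by sex, it may bias both the dyslipidaemia and the gender estimates.

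The text itself settles only the anaemia choice. On HDL and on the connector it stands one statement against one, so the documents do not show which version was intended. This should be corrected before analysis; it does not invalidate the design.

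**What to change.** Before analysis:

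1. Change the anaemia rule in the laboratory section to match the primary outcome definition (<12 g/dl for women, <13 g/dl for men).
2. Have the sponsor check the sex-specific HDL cut-offs against its own source, then state one version in both Table 2 and the laboratory section.
3. Write one explicit rule for dyslipidaemia that says which criteria are joined by *and* and which by *or*, and whether patients already on lipid medication count. Use it in both places.
4. Apply the single definitions to every patient, including the 92 already recruited, from the measured laboratory values.
5. As minor clean-up, align the sodium and potassium limits and correct the ejection fraction wording in Table 1.

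The cost is wording plus a reclassification. The laboratory section lists haemoglobin and all four lipid fractions among the tests run, so no new sampling should be needed. The article does not say that the lipid values themselves are entered in the dataset, and Table 2 lists dyslipidaemia as dichotomous. If only a yes/no code was kept, the values must be retrieved from the laboratory records.
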